## Abstract

**Background:**

Half of mental health disorders begin before the age of 14, highlighting the importance of prevention and early-intervention in childhood. Schools have been identified globally by policymakers as a platform to support good child mental health; however, the majority of the research is focused on secondary schools, with primary schools receiving very little attention by comparison. The limited available evidence on mental health initiatives in primary schools is hindered by a lack of rigorous evaluation. This quasi-experimental cluster study aims to examine the implementation and effectiveness of a Mental Health and Wellbeing Co-ordinator role designed to build mental health capacity within primary schools.

**Methods:**

This is a primary (ages 5–12) school-based cluster quasi-experimental study in Victoria, Australia. Before baseline data collection, 16 schools selected by the state education department will be allocated to intervention, and another 16 matched schools will continue as ‘Business as Usual’. In intervention schools, a mental health and well-being coordinator will be recruited and trained, and three additional school staff will also be selected to receive components of the mental health training. Surveys will be completed by consenting staff (at 2-, 5-, 10- and 17-months post allocation) and by consenting parents/carers (at 3-, 10- and 17-months post allocation) in both intervention and business as usual schools. The primary objective is to assess the change in teacher’s confidence to support student mental health and wellbeing using the School Mental Health Self-Efficacy Teacher Survey. Secondary objectives are to assess the indirect impact on systemic factors (level of support, prioritisation of child mental health), parent and teachers’ mental health literacy (stigma, knowledge), care access (school engagement with community-based services), and student mental health outcomes. Implementation outcomes (feasibility, acceptability, and fidelity) and costs will also be evaluated.

**Discussion:**

The current study will examine the implementation and effectiveness of having a trained Mental Health and Wellbeing Coordinator within primary schools. If the intervention increases teachers’ confidence to support student mental health and wellbeing and builds the capacity of primary schools it will improve student mental health provision and inform large-scale mental health service reform.

**Trial registration:**

The trial was retrospectively registered in the Australian New Zealand Clinical Trials Registry (ANZCTR) on July 6, 2021. The registration number is ACTRN12621000873820.

## Background

It is estimated that 10–17% of children and young people aged 4–17 years meet criteria for a mental health condition [1–3], and half of mental health conditions begin by the age of 14 [4]. While for some children certain behaviours might be developmentally appropriate and resolve over time without intervention, in others they suggest mental health disorders that if left unaddressed can have deleterious impacts across every aspect of a child’s life. In the short-term, children with mental health conditions have higher rates of school absenteeism [5], resulting in poorer learning outcomes [6]. Longer-term, poor childhood mental health has been associated with increased rates of unemployment, violence, substance misuse, suicide, poorer social functioning and a lower quality of life in adulthood [7].

There has been a marked increase in presentations to tertiary services of children with non-urgent mental health issues over the past 13 years [8]. This is likely to reflect a combination of low child mental health literacy among parents (leading to delayed recognition of the existence and/or severity of the child’s mental health problem) and barriers to accessing appropriate, community-based early intervention services (i.e., service fragmentation, difficulty navigating the mental health system and high costs and long wait times to access specialist care) [2, 9–12]. In an effort to provide children with more appropriate and timely support before mental health problems become entrenched, there has been a strong push internationally to implement preventative approaches to mental health issues in children [13].

Schools have been consistently flagged by policymakers and other stakeholders as an ideal universal platform to promote and support good mental health for all students, to identify and manage students with emerging mental health issues early, and to target interventions for students with significant mental health problems [13–16]. For students with and without mental health issues, school-based mental health services have been identified as the most common setting for mental health support [17]. This is especially true for minority populations and for students with less obvious mental health issues (i.e., internalising or subclinical symptoms) who are less likely to seek out care [18–20].

In the adolescent age group, there have been different approaches both within Australia and other countries to increase the support provided in schools [13, 21]. Approaches which demonstrate impact in building the capacity of secondary schools include refining pathways to care [22], whole school approaches to changing school culture [23], mental health literacy programs for staff [24] and students [25–27], services provided by community-based counsellors and clinical practitioners [28, 29] and third party delivered intervention programs [30]. However, despite this significant progress in secondary schools, [8], child mental health and the role of primary (children aged between 5 and 12 years old) schools has received comparatively little attention. This is particularly problematic given the trend towards mental health issues emerging before the age of 14 [4]. Factors such as adults’ limited knowledge regarding child mental health (i.e., child mental health literacy), a reliance on parent and carer engagement and consent to access care and a fragmented child mental health system may all impede progress in child mental health prevention and support within the primary school setting [31].

This gap in primary schools has been recognised by educators themselves; they acknowledge that student mental health and wellbeing support is part of their core role but consistently report feeling overwhelmed by the volume and complexity of issues, a lack of mental health literacy and confidence in their ability to address students’ mental health issues, insufficient time, training and resources and poor access to specialist services [32–35]. In Australia, there have been national [36], state [37], and local examples [23] of programs designed to improve mental health support in primary schools. However, initiatives have either relied on untrained, time-poor school-based staff to take on additional tasks such as acting as a wellbeing officer, or clinicians from outside the school system to deliver services, often for only the most complex or severe cases [38, 39]. Neither of these approaches addresses the capacity and service access barriers cited by educators.

Many primary school mental health initiatives lack rigorous evaluation of a program’s effectiveness or how effectively it has been implemented in the school context [40]. Where there has been effort across the sector to evaluate programs, often this is done retrospectively or using cross sectional designs which fail to capture change over longer periods of time [41]. This has resulted in an incomplete evidence base regarding the sustainability of implementation and program outcomes. Further, the lack of a control comparison in many evaluations means it is not possible to conclude if the program has produced benefit over and above what is already occurring in the school. Only 33% of evidence-based programs are successfully implemented into practice [42], largely due to a lack of consideration paid to implementation strategies. To achieve successful, long-term sustainability of mental health initiatives in a complex multi-level system, it is important that key implementation principles be embedded within the design. In an education context, this requires program designers to consider not just the intervention and the individual, but also the *inner* (immediate school environment) and *outer settings* (region/district and the larger political, social and economic context) [43].

The primary school age period presents a unique opportunity to intervene early and modify the trajectory of many mental health issues and prevent progression to more chronic conditions. The intervention in this study has been designed to leverage this developmental window and address the gaps in the school-based child mental health system by introducing the concept of a Mental Health and Wellbeing Coordinator (MHWC) role in primary schools. The MHWC is an experienced qualified educator who will be an *additional* resource for the schools and will take up their role alongside participation in a comprehensive training program designed within an implementation science framework. The role and the training program combine to form the “The MHWC model”, which aims to build mental health capacity within the school. The MHWC will be trained to identify mental health issues, establish clear referral pathways, work proactively with other professionals, and implement whole-school approaches to mental health and wellbeing. This will equip schools and classroom teachers with an additional resource for supporting student mental health and wellbeing. In addition, the MHWC will act as the liaison between the school and community-based health and other community-based services.

The primary objective of this study is to assess whether the MHWC model leads to changes in classroom teachers’ self-reported confidence to support student mental health and wellbeing. Secondary objectives are to investigate the indirect impact on systemic factors (level of support, prioritisation of child mental health), parent and teachers’ mental health literacy (stigma, knowledge), care access (school engagement with services), and student mental health outcomes. Implementation outcomes (feasibility, acceptability, and fidelity) and costs will also be evaluated.

## Methods

### Design and setting

The study is a quasi-experimental cluster study involving 16 intervention and 16 control (Business and Usual [BAU]) schools (Fig. 1). We will use a multi-method (qualitative and quantitative data), multi-site and multi-informant (MHWCs, school leaders, teachers, education support staff, parents/carers) design. This study has been approved by the Royal Children’s Hospital Human Research Ethics Committee (#65924) and the Victorian Department of Education and Training’s (DET) Research in Schools and Early Childhood settings (RISEC) process (#2020_004332).

**Fig. 1 Fig1:**
[figure not shown]
Flow chart estimating the progress of schools and participants through trial. *Staff surveys will be completed by MHWCs (intervention schools only) and school staff (school leaders, classroom teachers, education support staff)

iData collection will occur over six timepoints in both intervention and BAU schools beginning at timepoint 1 (T1; 2 months post allocation) and continuing through to timepoint 2 (T2, 3 months), timepoint 3 (T3, 5 months), timepoint 4 (T4; 6 months – intervention schools only), timepoint 5 (T5; 10 months) and timepoint 6 (T6; 17 months).

### Recruitment and participants

#### Schools

DET will recruit 16 intervention schools to receive the MHWC model from the North West (NW) and South West (SW) regions of Victoria, Australia in November 2020 (Fig. 1). Schools will be recruited by DET based on mental health need (through consultation with regional stakeholders and Incident Reporting Information System (IRIS) data), readiness (ensuring schools have the capacity and willingness to participate) and context diversity (including metropolitan, regional and rural contexts, and those impacted to different degrees by COVID-19). A comparison group of schools matched for socio-economic status (SES), location (metropolitan, regional, rural, remote) and number of student enrolments will be recruited by the research team and will act as controls (Business as Usual [BAU] schools). Secondary schools (ages 12–20), specialist schools (i.e., schools teaching specialist subjects or specialise teaching students with disability), and schools located outside NW, and SW regions of Victoria will be excluded. All participating schools will complete a formal consent process; details of what is required for schools to participate in the study will be outlined by the research team to the school Principal in a school plain language statement. An online consent form with the school plain language statement will be completed by the Principal or Assistant Principal prior to participant recruitment.

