#### Participant demographic characteristics and professional experience

Basic demographic information will be collected via survey, including participant age, school postcode, highest level of education, languages spoken at home, the number of years teaching and/or working within primary schools (school staff only), previous participation in child mental health and wellbeing related training courses and professional development (school staff only).

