### Implementation measures

#### Readiness to implement

To effectively evaluate the implementation of the MHWC model we will also seek to understand individual and contextual characteristics (across all participant groups) that are present prior to implementation which may also influence program outcomes. We will use the Readiness to Implement Scale [51] which looks at three key areas: feasibility, fit and staff support. It is a self-report measure, consisting of 20 items and has an overall reliability of Cronbach’s alpha [α] = .92 [51].

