### Planned statistical analysis

All analyses will be based on observed data only; i.e. we will assume data are Missing Completely At Random. We will make every attempt to ensure that data are not missing from surveys at the point of completion. If there are missing responses to surveys completed by school or regional staff, we will follow up via phone or email up to three times to obtain the missing responses. If missing data are > 10% for specific outcomes, then predictors of missing data will be explored and sensitivity analyses making further adjustments (i.e. valid under Missing At Random) will be used such as imputation. The details of how this will be conducted will be outlined in the statistical analysis plan.

The primary outcome (mean difference in SMH-SETS total score) will be analysed using mixed effects linear regression fitted at the teacher level, including a fixed effect for arm (MHWC vs. BAU) and a random effect for school, adjusting for baseline values of SMH-SETS and school matching criteria (ICSEA, number of enrolments and metro/regional/rural location).

According to the nature of the secondary outcomes to be analysed (binary, continuous or ordinal) the appropriate mixed effects model will be used to estimate the impact of the MHWC model on the outcome of interest compared to the BAU schools. These models will be fitted at the participant level, including a fixed effect for arm (MHWC vs. BAU) and a random effect for school adjusting for school matching criteria (ICSEA, number of enrolments and metro/regional/rural location) and baseline value of the outcome where available. Analyses will be done using Stata Statistical Software MP.

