## Discussion

This study protocol introduces a quasi-experimental cluster study investigating the impact of a mental health and wellbeing coordinator (MHWC) model on classroom teacher confidence to support student mental health and wellbeing in an Australian primary school setting. Previous approaches have largely focussed on developing and evaluating specific mental health and wellbeing programs delivered using existing school resources in cross-sectional study designs with limited attention paid to implementation factors [38]. This protocol describes a novel approach to building the capacity of primary schools by introducing an additional resource for schools, the MHWC, which is embedded through an implementation science framework to maximise impact on target outcomes and long-term sustainability.

Despite the strengths of the proposed study, there are some practical limitations involved in conducting applied research in a school setting [60]. First, a randomised controlled trial (RCT), the gold standard for assessing effectiveness of an intervention, was not feasible in the current study as intervention schools were selected by DET based on mental health need, readiness and context diversity [61]. The quasi-experimental design does have the benefit of enabling enrolment of schools to the intervention based on motivation, which reflects the real-life situation of public health interventions. The lack of randomisation, however, can introduce both selection bias and confounding. We will aim to mitigate these biases by matching our control schools and adjusting for known confounders as well as T1 values at the analysis level.

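### Mental health need and readiness decide which schools enter the intervention arm, but neither is matched or adjusted for, so residual confounding by both is not addressed although the Discussion says known confounders will be adjusted for

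*Protocol article*

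**What the plan says.** **Selection of intervention schools.** In the Schools subsection of Recruitment and participants, the education department chooses the 16 intervention schools: "Schools will be recruited by DET based on mental health need (through consultation with regional stakeholders and Incident Reporting Information System (IRIS) data), readiness". Readiness is explained as "ensuring schools have the capacity and willingness to participate". Context diversity is the third criterion. The Discussion repeats all three as the reason randomisation was not feasible.

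**Selection of controls.** The same subsection describes "A comparison group of schools matched for socio-economic status (SES), location (metropolitan, regional, rural, remote) and number of student enrolments". These schools "will be recruited by the research team and will act as controls (Business as Usual [BAU] schools". The education department does not choose them.

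**Model.** Planned statistical analysis specifies a mixed model at the teacher level with a random school effect, "adjusting for baseline values of SMH-SETS and school matching criteria (ICSEA, number of enrolments and metro/regional/rural location". Secondary models use the same school criteria, and the baseline value only where there is one.

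**Stated mitigation.** The Discussion concedes that selection bias and confounding are possible and says the authors will aim to "mitigate these biases by matching our control schools and adjusting for known confounders as well as T1 values at the analysis level".

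**Data collection.** The Readiness to implement subsection speaks of "individual and contextual characteristics (across all participant groups) that are present prior to implementation" and says these may influence outcomes. Table 2 ticks the scale for coordinators, trainees and intervention staff only. The section on participant demographics covers school staff generally, including "previous participation in child mental health and wellbeing related training courses and professional development (school staff only", but the demographics row of Table 2 has no tick for Business as Usual (BAU) staff.

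**The concern.** Without randomisation, matching and covariate adjustment are the main protection for the arm comparison. A variable that determines allocation and also predicts the outcome confounds that comparison. The protocol names two variables that determine allocation, and neither appears in the matching or the models.

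The baseline SMH-SETS score removes differences in starting level so far as T1 captures them. It does not remove differences in later change. A school chosen because it is willing and has capacity might gain confidence faster without a coordinator. A school chosen for high need might have more room to improve, or might be under more strain. T1 is also 2 months after allocation, so it may not be a clean pre-intervention value.

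The primary estimate is meant to inform state and national roll-out. A reader of the Discussion would believe the known selection factors had been handled.

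**Working it through.** **1. Selection factors against the adjustment set**

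| Factor | Drives selection | Matched | In primary model |
|---|---|---|---|
| Mental health need (stakeholders, IRIS) | yes | no | no |
| Readiness (capacity, willingness) | yes | no | no |
| Context diversity | yes | partly, through location | partly, through location |
| SES / ICSEA | not named | yes | yes |
| Enrolments | not named | yes | yes |
| Baseline SMH-SETS | not named | no | yes |

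The covariate list is stated explicitly. The only detail that section leaves to the analysis plan is the handling of missing data.

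**2. The plan's own figure**

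Inputs from Sample size calculation: 16 schools per arm, 12 teachers per school, ICC 0.1, SD 9.5, difference 3.9, two-sided 5%.

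- Design effect = 1 + (12 − 1) × 0.1 = 2.1
- Effective n per arm = 16 × 12 / 2.1 = 91.43
- SE = 9.5 × √(2/91.43) = 1.405
- Power = Φ(3.9/1.405 − 1.96) = 79.3%, against 80% stated
- Detectable difference at 80% power = (1.96 + 0.842) × 1.405 = 3.94, against 3.9 stated

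The figure reproduces. It takes the arm difference as unbiased.

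**3. What a residual bias would do (illustration, not an estimate)**

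The document gives no size for the confounding. Assume one school-level factor differs by 1 SD between arms and has standardised association b with follow-up SMH-SETS after adjustment.

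- Bias B = b × 1 × 9.5 points
- False-positive rate with no true effect = Φ(B/SE − 1.96) + Φ(−B/SE − 1.96)
- Share of between-school variance the factor must explain = b² / ICC = b² / 0.1

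| b (assumed) | Bias, points | False-positive rate | Share of between-school variance |
|---|---|---|---|
| 0.05 | 0.48 | 6.3% | 2.5% |
| 0.1 | 0.95 | 10.4% | 10% |
| 0.2 | 1.90 | 27% | 40% |
| 0.3 | 2.85 | 53% | 90% |

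The last column limits what is credible. Between-school variance is 0.1 × 9.5² = 9.0. At b = 0.3 the factor alone would account for 0.09 × 90.25 = 8.1 of it, before T1, ICSEA, enrolments and location take their share. That row is close to a ceiling, and the 0.2 row is already demanding.

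**4. Cost of one more school-level covariate**

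- School-level degrees of freedom now: 32 − 6 = 26 (intercept, arm, ICSEA, enrolments, two location indicators). One more covariate leaves 25.
- If need differs by d SD between equal arms, r² with arm = d²/(d² + 4).
- d = 0.5: r² = 0.25/4.25 = 0.059, variance inflation 1/(1 − 0.059) = 1.06, detectable difference 3.94 × √1.06 = 4.06
- d = 1: r² = 1/5 = 0.20 (r about 0.45), variance inflation 1.25, detectable difference 3.94 × √1.25 = 4.40

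These losses assume need explains none of the outcome. Any variance it does explain gives some precision back.

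**The case against.** The protocol does not hide the problem. It concedes selection bias and confounding and claims only an aim to mitigate them. Both arms come from the same two regions. Baseline SMH-SETS, itself a teacher-level covariate, is in the primary model, and ICSEA may partly stand in for need. This stands, and it limits the point to residual confounding.

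Several stronger readings are tempting, and the document does not support them.

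- *The arm effect carries the full selection bias.* Part of it is removed by the baseline score, ICSEA, enrolments and location.
- *The bias is large and favours the intervention.* Neither size nor direction can be derived. Readiness would probably favour the intervention, but need could act either way, and a bias near 2.85 points would use up almost all the between-school variance that the assumed ICC allows.
- *Table 2 rules out any repair.* It limits survey data. IRIS is administrative data that the education department already used for selection.
- *BAU staff should complete the readiness scale so that it can be adjusted for.* The scale covers feasibility, fit and staff support for implementation, and BAU schools have no model to rate. Nothing shows that a generic part exists. Scores taken 2 months after allocation may already reflect having been chosen.

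It may also be said that BAU schools consent too. They consent to being studied, not to hosting the role and training, so this is not the same readiness. Re-matching is probably too late, since intervention recruitment was set for November 2020 and the Discussion says schools were selected. A covariate in the analysis does not depend on re-matching.

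**Conclusion.** The point holds as one of residual confounding. Need and readiness are the protocol's own stated drivers of allocation, and both are absent from the matching and from the models. The Discussion's statement about known confounders is therefore not met for them. Secondary outcomes without a baseline value have less protection still.

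The size and direction of the bias are unknown, and the table of assumed biases shows only that a modest one matters: 0.1 SD would double the nominal 5% error rate. This does not make the comparison invalid. It calls for one inexpensive covariate and a more exact statement of what is left unadjusted.

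The mismatches between Table 2 and the text on demographics and on the readiness scale are minor consistency faults. The demographics gap could simply be a missing tick.

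**What to change.** 1. Ask the education department for IRIS incident counts from before November 2020 for all 32 schools, expressed per enrolled student. Add the rate as a school-level covariate in the primary and secondary models. At the least, prespecify a sensitivity analysis with it and report that beside the primary result.
2. Reword the Discussion to say that readiness and the stakeholder-judged part of need, which incident rates cannot capture, are not adjusted for and remain possible confounders.
3. Reconcile Table 2 with the section on participant demographics, so that demographics, years of teaching and prior training are collected from BAU staff as well.
4. Reconcile Table 2 with the Readiness to implement subsection on who completes that scale.

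Cost: one administrative data request, one school-level degree of freedom (26 to 25), and variance inflation of about 1.06 to 1.25 if need differs by 0.5 to 1 SD between arms. The rest is wording.

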#### Mental Health and wellbeing coordinator (MHWC) role

For each intervention school, a MHWC will be employed and funded a full-time equivalency (FTE; outlined below). To be recruited for this role the MHWC should have a teaching qualification and registration with the Victorian Institute of Teaching. Once recruited the MHWC will:
Receive evidence-based training around supporting the mental health needs of primary school students;Embed evidence-based training and professional development (Tier 1 practices & frameworks) across the school and build the capability of teaching and education support staff to better identify and support students with mental health issues;Be a significant contributor to the school’s wellbeing team;Support the referral pathway for students identified as requiring further assessment and intervention within the school or to external community-based services (the MHWC role will not involve providing 1:1 counselling support to students);Work proactively with regional staff (i.e., psychologists, speech and language therapists, social workers), school wellbeing and leadership teams, and other health professionals (community-based psychologists, paediatricians, GPs, other allied health) to engage appropriate mental health support such as assessment, counselling, classroom based adjustments;Connect wellbeing initiatives across the school and be responsible for implementing whole school approaches to mental health and wellbeing, including the social and emotional learning curriculum.

MHWC full time equivalency (FTE) allocation will be determined based on number of student enrolments at each school using the following scale: 0–149 students = 0.4 FTE, 150–299 students = 0.6 FTE, 300–449 students = 0.8 FTE, > 449 students = 1.0 FTE. An additional loading will be provided for MHWCs working in regional and rural schools.

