## Primary and secondary outcomes and measures

### School and participant characteristics

#### School characteristics

Information will be collected for each school including the Index of Community Socio-Educational Advantage (ICSEA) [54] metropolitan, regional, rural or remote location as determined by DET, number of enrolments and region (NW or SW).

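### NW/SW region limits eligibility and is recorded for every school, but it is neither a matching factor nor in the stated adjustment set of this non-randomised comparison

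*Protocol article*

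**What the plan says.** In the protocol article, the section on schools sets the catchment: "DET will recruit 16 intervention schools to receive the MHWC model from the North West (NW) and South West (SW) regions of Victoria". It adds that "schools located outside NW, and SW regions of Victoria will be excluded". The education department chooses the intervention schools on need, readiness and diversity of context. On need, the text reads: "Schools will be recruited by DET based on mental health need (through consultation with regional stakeholders and Incident Reporting Information System (IRIS) data".

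The research team recruits the controls, described as "A comparison group of schools matched for socio-economic status (SES), location (metropolitan, regional, rural, remote) and number of student enrolments". NW or SW is not on that list.

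Under school characteristics, the items collected include "metropolitan, regional, rural or remote location as determined by DET, number of enrolments and region (NW or SW". Location type and region are thus two separate variables.

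Under planned statistical analysis, the primary model is a mixed linear regression with a random school effect, "adjusting for baseline values of SMH-SETS and school matching criteria (ICSEA, number of enrolments and metro/regional/rural location". Secondary models use the same school factors, with baseline where available. The moderator section also uses location type rather than NW/SW. The discussion concedes selection bias and confounding, and relies on matching plus adjustment for known confounders and T1 values, without naming region.

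**The concern.** Location type does not stand in for region. A metropolitan school in NW can be matched to a metropolitan school in SW and still satisfy every stated criterion. One body selects the intervention schools and another the controls, and neither process carries a rule that balances NW against SW. Nothing in the design therefore makes the regional mix of the two arms equal.

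The protocol gives some grounds for treating region as relevant. Its background counts region/district as part of the outer setting that programme designers should consider. The coordinator's duties include "Work proactively with regional staff (i.e., psychologists, speech and language therapists, social workers". Some secondary outcomes concern support from the department and engagement with its services, which regional provision could plausibly affect.

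The planned adjustment would not fully deal with a regional difference. The T1 score absorbs part of a stable difference between regions but not divergence after T1, and some secondary outcomes may have no baseline. A random effect for school models clustering; it does not remove confounding by a school-level variable. If the arms had different regional mixes, part of a regional difference would be read as an effect of the MHWC model, or would mask one.

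**Working it through.** **The plan's own figure first.** Inputs from the sample size section: SD 9.5, 12 teachers per school, ICC 0.1, 16 schools per arm, two-sided 5%, target 3.9.

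- Design effect = 1 + (12 − 1) × 0.1 = 2.1.
- Effective n per arm = 16 × 12 / 2.1 = 91.4.
- SE of the arm difference = 9.5 × √(2/91.4) = 1.405.
- Power at 3.9 = 79.3% (normal approximation). Detectable difference at 80% power = (1.960 + 0.842) × 1.405 = 3.94.

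The stated 80% reproduces. Nothing here disputes it; 1.405 and 3.94 are used as the yardstick.

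**Bias from leaving region out.** Let p1 and p0 be the NW shares of the intervention and BAU arms. Let δ be the NW–SW difference in outcome that remains after ICSEA, enrolments, location type and T1 score. Then

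bias = (p1 − p0) × δ.

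The document gives neither the split nor δ. Both are assumptions, with δ taken from 1 to 3.9 points. The type I error treats the bias as a shift of bias/1.405 in the test statistic.

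**Cost of putting region in.** If r is the correlation between arm and region across the 32 schools, the variance of the arm effect is multiplied by 1/(1 − r²). The detectable difference becomes 3.94 × √(1/(1 − r²)), before any variance that region itself explains. For 12/6: pooled share 18/32 = 0.5625; r = 0.375 × 0.5 / √(0.5625 × 0.4375) = 0.378; r² = 0.143; factor 1.167; 3.936 × 1.080 = 4.25.

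| NW schools of 16, MHWC/BAU | p1 − p0 | Bias, δ = 1 | Bias, δ = 3.9 | Type I error, δ = 1 to 3.9 | Variance factor with region | Detectable difference with region |
|---|---|---|---|---|---|---|
| 8/8 | 0 | 0 | 0 | 0.050 | 1.000 | 3.94 |
| 9/7 | 0.125 | 0.13 | 0.49 | 0.051–0.064 | 1.016 | 3.97 |
| 10/6 | 0.250 | 0.25 | 0.98 | 0.054–0.107 | 1.067 | 4.07 |
| 12/6 | 0.375 | 0.38 | 1.46 | 0.058–0.180 | 1.167 | 4.25 |
| 12/4 | 0.500 | 0.50 | 1.95 | 0.065–0.284 | 1.333 | 4.55 |

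**How demanding is the upper end?** With ICC 0.1, the between-school variance is 0.1 × 9.5² = 9.03. With half the schools in each region, a regional difference δ contributes δ²/4 to it: 0.25 (3%) at δ = 1 and 3.80 (42%) at δ = 3.9. A residual difference near 3.9 is arithmetically possible, but it would make region a dominant source of variation between schools. The right-hand end of the bias range should be read as extreme.

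**The case against.** The strongest reply is that the plan is internally consistent. It matches on three school factors, adjusts for those factors and baseline, admits the risk of confounding, and restricts both arms to the same two regions, which already controls region in part. No passage says that NW and SW differ on anything that affects the outcome, and none shows an unequal split. On this view, the choice of covariates is a matter of preference, and the plan could still tabulate or adjust for region later.

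Much of that stands. Harm is possible, not shown; its direction is unknown; and no stated number is wrong. Two stronger readings should also be set aside:

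- A reader might infer that schools were nominated by region. The text says only that the department recruits from two regions and consults regional stakeholders about need. It describes no regional nomination or quota.
- A reader might infer that the discussion describes differing regional responses to the Royal Commission or to COVID-19. It speaks of programmes implemented by individual schools, says actions will be collected for each school and considered in interpretation, and draws no NW/SW contrast.

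It is also fair to say that a region term costs more than one degree of freedom when the arms are imbalanced, as the table shows.

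What does not stand is that the matter is simply left open. The article names the adjustment set for the primary and secondary models and defers only the missing-data details to the statistical analysis plan. Restricting both arms to two regions does not equalise the mix within them. The precision cost is negligible near balance and grows only as omission becomes riskier.

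**Conclusion.** The point holds as a modest weakness in the choice of matching factors and covariates. It is neither a contradiction nor a numerical error. Bias needs two things together: an unequal NW/SW split, and a regional difference that remains after the planned covariates and T1 score. The document establishes neither, and with equal splits the bias is zero.

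Under the assumed splits of 9/7 to 12/4 and residual differences of 1 to 3.9 points, the bias is about 0.1 to 2.0 points, or 3% to 50% of the 3.9-point target (0.125/3.9 and 1.95/3.9). The upper end needs both a severe imbalance and a very large regional difference. These figures describe the exposure; they do not estimate an actual bias. They use the plan's SE of 1.405, which takes no credit for baseline adjustment.

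**What to change.** - If matching is still open, require each control school to come from the same region (NW or SW) as the intervention school it is matched to. This narrows the pool of candidate controls somewhat.
- If matching is done, tabulate region by arm and add region (NW/SW) as a fixed effect beside ICSEA, enrolments and location type in the primary and secondary models. At minimum, prespecify this as a sensitivity analysis.

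The variable is already collected, so no new data are needed. The cost is one school-level degree of freedom out of 32 schools, plus the precision loss tabulated above if the arms turn out imbalanced: negligible at or near balance, and a detectable difference of about 4.07 at 10/6, 4.25 at 12/6 and 4.55 at 12/4.
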